**Randomization technique and Blinding**

We selected 20 clusters randomly from eligible 80 from four districts in the region and allocated them into intervention and control in 1:1 allocation,10 each to the intervention and control cluster. To balance based on the distance of clusters from nearby health facilities between intervention and control clusters, we used stratified first the 20 clusters into four categories based on the population size and distance to the nearest health facility to reduce confounding. The four strata were: 1) Higher population (over 4,000 residents) and longer distance (more than an hour of walking distance), 2) Higher population and shorter distance (less than an hour walking distance 3) Lower population (less 4,000 residents) and shorter distance and 4) Lower population and longer distance. Then clusters from each stratum were randomly allocated to intervention and control using a computer-generated random number using simple randomization. A seed number was produced and sent from a university of Bergen as a starting point for random number generation. Blinding is difficult because of the nature of cluster randomized trials, but we created a buffer zone between intervention and control clusters to reduce intervention contamination. Data collectors are independent of the intervention process and do not have formal information on which study arm the cluster to which they collect data belongs.

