The main responsibility of the COLs is identifying problem such as barriers hindering mothers and babies receiving important health care and fall out of the continuum of care. They respond to the problem coordinating local collective efforts, for example transport or financial support to reach a health facility and taking care of the family members at home. For this contribution, they meet every two-weeks to evaluate and re-plan their actions based on the principles of Participatory Learning and Action (PLA) model (21). WDTs help COLs with gathering and providing sub-village information. COLs use their high level of acceptance to visit and support families where the relationship between the woman and her husband is not smooth and put great pressure on the health and wellbeing of women or their newborns. At such households, COLs provide essential advice on the importance of care for a pregnant women and newborn babies. This is expected to contribute to a mother and baby receive essential care that improve their survival and wellbeing.

The project provides training and supervision support to the three key stakeholders participating in intervention.

For COLs, the training and supervision will be based on PLA model of problem identification, providing local solutions, evaluating the effect, and re-planning process. COLs receive a day-long initial training and a two-monthly supervision discussion for an hour during the project period.

Trainings and supervision to HEWs will have two dimensions: On one hand, HEWs will be trained and supported on technical refresher issues related to baby resuscitation and home-based immediate support when a birth occurs at home, and essential postnatal maternal and newborn care and on the other hand, they will be trained on leadership role to lead the efforts of COLs and WDTs. HEWs receive two days of intensive training followed by two-monthly supervision and monitoring meetings with the project team.

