The training and supervision of WDTs will be mainly on identifying and connecting mothers and babies for normal essential care as well as detecting danger signs and referring for emergency care babies and mothers with severe sickness (danger signs). In addition, WDTs receive training on maternal essential self-care, preparation for healthcare, nutrition, rest, hygiene, and other important information which in turn they will teach mothers and families. Further, the WDTs receive training on tracking and giving special attention to high-risk mothers and babies in difficult families and hard-to-reach villages so that they are not left out or fall out of the critically needed healthcare services. Through these mechanisms, the project builds a supportive network around mothers to help improve the initiation and completion of essential services in the continuum of care around pregnancy and childbirth. Table 2 below describes the roles of each stakeholder to the four mechanisms of actions to improve continuum of care in the intervention clusters.

Table 2: The role of stakeholders in the community-based actions in intervention clusters

|  | 1. Identify and connect | 1. Educate and prepare | 1. Support through collective efforts | 1. Home-based essential care |
| --- | --- | --- | --- | --- |
| HEWs | All pregnant mothers for essential ANC, delivery, and postnatal care in collaboration with HDTs and COLs  Mothers and babies in high-risk of falling out of care, or even do not initiate first contact.  Screen and recruit mothers for study 20-26^th^ week of gestation. | Mothers and families on essential care, nutrition, hygiene…  Prepare mothers and family for facility delivery, emergency health seeking. | Mainly through coordinating the efforts of COLs | Encourage antenatal care as per the guidelines of MoH  Emergency maternal and newborn help for deliveries occurred at home.  Routine postnatal care for mothers and babies. |
| HDTs | Identify mothers and babies in her sub-village and connect to HEWs, COLs and health care.  Guide data collectors to locate homes. | Educate and prepare mothers and families on essential care, nutrition, hygiene, emergency care | Inform to COL s and HEWs about mothers and babies not receiving care | Educate and prepare.  Do not provide any technical care. |

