**Outcome and process indicators**

The primary maternal outcome measure is the completion rate of essential maternal care. We define a continuum of care completion as follows:

1. fully completed care when a mother has received four or more antenatal care, delivered in a health facility with a skilled attendant, and received at least four postnatal care (first 24 hours, 48-72 hours, 7-14 days, and six weeks after delivery) from HEWs or other health professionals within the first month after delivery. Because maternal completion of these essential care components will have an implication for newborn health and survival, and essential newborn care is given simultaneously during delivery and postnatal care, the completion of essential newborn care will be analyzed in relation to the maternal completion rate.
2. Emergency home-based care when the delivery occurred at home and mother and baby received immediate visit at home by HEWs or a higher health professional.
3. Sub-analysis on the primary outcome will compare intervention with control clusters separately on antenatal care completion rate, rate of facility delivery, proportion of assistance received immediately form HEWs or other professionals when a birth occurred at home, and proportion of mothers who stayed at maternal waiting shelters immediate days before delivery.
4. Proportion received financial, transport, and family care support from community resource persons (COLs) when a support is critically needed.
5. The proportion of newborn babies received the four essential newborn care services (immediate and thorough drying, skin-to-skin contact, immediate breastfeeding initiation, and delayed cord clamping)
6. Emergency newborn sickness identification and referral rates.
7. Secondary outcome measure will be on whether the intervention affected reduction of neonatal mortality and stillbirth rates.

For newborn babies, we will measure and compare with the control arm the proportion of babies immediately put to breastfeeding and exclusively feeding until at least a month after birth, the proportion of babies received essential thermal care (wrapping in close, skin-to-skin contact to mother immediately, delayed baby bathing), baby resuscitation at home and in clinics, and proportion of babies received emergency treatment and referrals when they had danger signs.

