**Data collection**

Data will be collected by trained independent data collectors a maximum of five times at households and from health facility records.

First, we will collect data when the mother’s gestation is 20th to 26th week when she formally recruited for subsequent follow-up. This period matches with the time when a mother became pregnant after the start of the intervention process in the intervention cluster. In other words, the mothers who enter the first data collection and follow-up phase on their 20th to 26th week of gestation has been exposed to interventions since they were pregnant. In this first round of data collection, data will be collected on basic socio-demographic and important variables for important covariates such as wealth status indicators, distance to health facility, history of healthcare utilization during the previous pregnancy and delivery.

Follow-up data collection will include the second to the fifth rounds of data collection. The second round will be 10 weeks after the first data collection (30^th^ to 36^th^ week of gestation). This data collection will mainly focus on information about variables related to the continuation of antenatal care utilization and whether the mother had pregnancy related complications and severe sickness, including information on received healthcare for sickness.

The third round of data collection is on the fourth day after delivery. The main variables in this round of data collection include variables on antenatal care completion, delivery information such as place of delivery, delivery attendant, utilization of postnatal care during the WHO recommended first 24 hours and 48-72 hours after birth, whether the mother received any financial, transport, or family care support from the COLs support system to reach to health facility, whether the mother stayed in the maternal waiting shelter nearby health facilities the immediate days before delivery, delivery outcome (livebirth or stillbirth). Additional information will include about maternal and newborn complications during delivery, essential newborn care provided during delivery (resuscitation, umbilical care, thermal care, initiation of breastfeeding, treatment for severely sick and premature babies).

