**Data entry and analysis plan**

Data will be double entered into excel sheet and transferred to R software version 4.4.1for analysis (27). Data will be analyzed and presented in a format comparing outcomes between intervention and control arms using intention-to-treat analysis, meaning all recruited will be analyzed irrespective of finishing the study process. Data analysis will use techniques that consider the clustered nature of the data.

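### Women are recruited after allocation, by project-trained health extension workers in intervention clusters and by an unnamed recruiter in control clusters, so who enters can differ by arm

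*Protocol*

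**What the plan says.** Under Randomization technique and Blinding, 20 clusters have been allocated, 10 per arm. Under Participants, women are recruited at 20 to 26 weeks of gestation in June to September 2024. Data collection adds that these women will by then have been exposed to the intervention from early pregnancy.

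The stakeholder table in the Intervention section (Table 2) is titled "The role of stakeholders in the community-based actions in intervention clusters". Its HEW row includes "Screen and recruit mothers for study". The same section says of their preparation: "HEWs receive two days of intensive training followed by two-monthly supervision and monitoring meetings with the project team". The primary composite in Outcome and process indicators counts postnatal contacts "from HEWs or other health professionals within the first month after delivery". No section says who recruits in control clusters.

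On masking: "Data collectors are independent of the intervention process and do not have formal information on which study arm" their cluster belongs to. In the same Table 2 the women's groups (HDTs there, WDTs in the text) are to "Guide data collectors to locate homes". The third interview asks "whether the mother received any financial, transport, or family care support from the COLs support system".

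The analysis is by intention to treat, "meaning all recruited will be analyzed irrespective of finishing the study process".

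**The concern.** Cluster randomisation balances clusters. It balances the enrolled women only if they are found and enrolled in the same way in both arms. Here the recruiters in one arm deliver the intervention, know the allocation, and provide part of the care that is scored.

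The package also changes who is found. Women's groups are trained to track high-risk and hard-to-reach mothers, HEWs look for women who have not started care, and opinion leaders (COLs) identify further such women.

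Two opposite selections are possible. Bringing in more women who are unlikely to complete care lowers the intervention rate and can hide a benefit. Enrolling mainly women who are easy to follow raises it and can imitate one. Intention to treat keeps each woman in her cluster's arm once she has entered; it cannot repair a difference in who entered.

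**Working it through.** **The plan's own figure.** Inputs from Sampling strategy and sample size: 20% v 30%, z = 1.96 and 0.84, m = 150, ICC = 0.01.
- Individual n = (1.96 + 0.84)² × (0.2×0.8 + 0.3×0.7) / 0.1² = 7.84 × 0.37 / 0.01 = 290.1 per arm.
- Design effect = 1 + (150 − 1) × 0.01 = 2.49, giving 722.3 (723.1 with unrounded z). The stated 723 is reproduced. The printed bracket, taken literally, would give 290.1 × 150 × 0.01 = 435, so it is a typographical slip.

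**Sensitivity of the planned trial.** With 1000 per arm, or 100 per cluster, the design effect is 1 + 99 × 0.01 = 1.99 and the effective n is 1000 / 1.99 = 502.5 per arm. Power for 20% v 30% is about 96%, so a modest selection effect can be declared a treatment effect.

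**Illustration of selection (assumed; the protocol gives no selection rates).** True completion is 20% in both arms. In the intervention arm only, likely non-completers are recruited r times as often as likely completers. Observed rate = 0.2 / (0.2 + 0.8r). Rejection is by a two-sided 5% normal test on the effective n.

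| r | Observed rate | Chance of rejection |
|---|---|---|
| 1.00 | 20.0% | 5% |
| 0.95 | 20.8% | 6% |
| 0.90 | 21.7% | 10% |
| 0.75 | 25.0% | 48% |

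For r = 0.75: null SE = √(2 × 0.225 × 0.775 / 502.5) = 0.0263, and the threshold is 1.96 × 0.0263 = 0.0516. The spurious difference is 0.050, so rejection is close to a coin toss. With r above 1 the sign reverses: r = 1.25 gives 0.2 / 1.2 = 16.7%.

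**How much room for selection is there?**
- The sample-size section expects 150 pairs per cluster, and 1000 per arm means about 100 enrolled. If all completers were kept, the most extreme rate is 30 / 100 = 30%, equal to the whole planned effect (about 96% rejection).
- Table 1 populations at 30 births per 1000, assuming women pass through a 6-week window over 4 months: 84,347 × 0.030 × (4/12 + 6/52.18) ≈ 1,134 eligible in intervention and, likewise from 87,830, about 1,181 in control. The extreme for the intervention arm is then 0.2 × 1,134 / 1000 = 22.7% (about 18% rejection).
- At the local rate of 22.8 per 1000 that the protocol also cites, the pools are about 862 and 898, below target. There is then little room to choose among eligible women, although incomplete finding could still differ by arm.
- With 1000 enrolled, r = 0.90 fits a pool of 1,134. The r = 0.75 case needs at least 1,250 eligible women (250 + 0.75 × 1,000 = 1,000).

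**The case against.** The strongest reply is in Participants: all eligible, consenting women are to take part. A true census would leave nothing to select. Data collection also ties formal recruitment to the independent collectors' first visit, so HEWs may only screen and refer. Both points reduce the risk. Neither removes it: 1000 per arm is a fixed target below the 150 per cluster expected, no count of eligible against enrolled women is described, and even a census of known pregnancies differs if pregnancies are found differently.

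Several stronger readings go beyond the text:
- A reader might infer that control clusters find women only by routine means. The protocol does not say so; control recruitment is simply not described, and those clusters have 35 HEWs and 560 health development teams.
- A reader might infer that HEWs are trained to trace pregnancies. Their stated training is clinical and in leadership. Training in tracking goes to the women's groups; identification is a listed HEW role only.
- A reader might infer that the masking statement is contradicted. It claims only that collectors have no formal information. Local guides and the COL questions undermine that masking without contradicting it. COL support is a listed outcome, so the questions belong in both arms.
- A reader might call the outcome purely self-reported, but facility records are used too.
- A reader might sketch a larger bias: completion of 20% among women in care and 2% among those not, with not-in-care shares of 10% in control and 40% in intervention, gives 18.2% v 12.8%, or −5.4 points. With 1000 enrolled from the pools above, the control share implies at most (100 + 181) / 1,181 = 24% of the pool not in care, and the intervention share at least 400 / 1,134 = 35%. Arms drawn from similar populations cannot meet both.

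**Conclusion.** The concern holds as a risk of differential recruitment. The text supports each link: entry after allocation and exposure, recruitment in intervention clusters by project-trained HEWs whose contacts count in the outcome, intensified finding of women in that arm, no named control recruiter, and an analysis set defined by recruitment.

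Neither the size nor the direction of any bias is shown. Under the assumed ratios, 0.90 gives 21.7% and about 10% false-positive risk; 0.75 gives 25.0% and about 48%, and requires a larger eligible pool than Table 1 and a rate of 30 per 1000 suggest. These rest on 20% true completion in both arms, an ICC of 0.01 and 100 women per cluster. The room for selection runs from almost none under a census to one third left out.

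This should be settled in the protocol itself. Later adjustment can address measured differences only.

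**What to change.** 1. Remove screening and recruiting from the HEW role in Table 2. State one identical procedure for both arms: routine HEW and HDT pregnancy lists are passed on, and the existing independent data collectors confirm eligibility and take consent at the round-one visit, enrolling either all eligible women or consecutive ones.
2. Log and report listed, eligible, approached and enrolled numbers per cluster and arm. Recruitment was due to start in June 2024, and the reference list shows an access date of 8 July 2024, so it may be under way or complete. In that case, reconstruct these counts.
3. Adjust the primary comparison, at least as a sensitivity analysis, for round-one covariates that pre-date exposure: wealth, distance, and care use in the previous pregnancy, with a separate category for first pregnancies.
4. Ask the COL items last within the round-three interview. Moving them to week six would cost recall on a listed outcome. This protects the round-three items only; rounds four and five stay open to informal unmasking.

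Cost: an amendment and some extra work for the existing data collectors. They are not said to visit every household, so the procedure relies on existing pregnancy lists and not on a new household census. Those lists may themselves be fuller in intervention clusters, which is why the counts must be reported by arm. Sample size is unchanged.

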# Methods and materials

**Methods**

**Setting**

This trial research project will take place in rural areas of Sidama, a regional state in southern part of Ethiopia. Sidama became an autonomous regional state in 2020, separating from the former Southern Nations, Nationalities, and Peoples Regional State (SNNPRS) which is divided into four new regional states between 2020 and 2023. Sidama is situated approximately 400 kilometers south of Addis Ababa with an estimated population of about 4.6 million people in 2023. The capital of the regional state is Hawassa. Still, more than 80 percent of the population lives in rural areas, where agriculture is the primary economic activity and access to quality healthcare services is limited.

In 2018, an empirical study in one of the districts in Sidama showed that fertility was lower than reported from national estimates with crude birth rate of 22.8 births per 1000 population and total fertility rate of 2.9 children per woman. Furthermore, the population is transitioning to a low-mortality and low-fertility rate (19). However, the United Nations projected crude birth rate for Ethiopia is 30.6 births per 1000 population in 2024 (20), far higher than the empirical findings.

[figure not shown]

Figure 1: The map of the study area within Sidama regional State, Ethiopia.

Table 1: Background demographic and health service characteristics of study population

| Background | Intervention | Control | Remarks |
| --- | --- | --- | --- |
| Total population in 2024 | 84 347 | 87 830 |  |
| Expected births in 2024^x^ | 2 530 | 2 634 |  |
| Number of existing health centers | 7 | 8 | some overlaps |
| Number of Health Extension Workers | 37 | 35 |  |
| Number of Health Developments Team | 545 | 560 |  |
| Average distance to health centers | 5.3 km | 5,1 km |  |
| *Note: ^X^ = annual birth rate (3% of population) multiplied by population* | | | |

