WDTs are about 30 voluntary groups of women in each cluster residing in sub-villages of clusters in Ethiopia, freely helping the works of HEWs. They have recognition from the government without getting paid. Because of their unique position closer to sub-villages, they have the unique opportunity to identify mothers as they become pregnant in their respective villages and connect to healthcare services. They also educate and prepare mothers and families for standard and emergency care. WDTs' main contribution to the intervention is actively identifying and connecting mothers and babies to essential standard care and emergency care when they observe danger signs. WDTs will give particular attention to high-risk and hard-to-reach mothers and newborn babies such as extremely poor, living in difficult topography and distant villages from the health facilities and HEWs stations as well as those with existing sicknesses and malnutrition. As such, the contribution of the village WDTs in the four mechanisms of action will be identifying and connecting, education and preparing and involving with COLs in strengthening financial, transport, and family care support through collective local efforts so that a mother or baby reaches to health facility and receives care.

Community opinion leaders (COLs) are key leaders who lead opinions such as approval of the importance of receiving healthcare services and coordinating local collective help mechanisms. COLs are a group of local leaders forming a committee which includes influential religious leaders, cultural leaders, local government administrative leaders, and leaders of local welfare scheme called IDIR in Ethiopia. IDIR is a local welfare system where families contribute financially or materially every month. This welfare system often shares serious costs during deaths and severe sicknesses.

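### In intervention clusters the volunteers who deliver the intervention are to guide data collectors to homes, with no matching procedure stated for control clusters; this weakens collector independence and risks arm-specific over-reporting

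*Protocol*

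**What the plan says.** - **Blinding** (Protocol, Randomization technique and Blinding). The protocol concedes that blinding is hard in this design and offers one safeguard at outcome collection: "Data collectors are independent of the intervention process and do not have formal information on which study arm" their cluster is in.
- **Home-finding** (Protocol, Intervention, second of two tables numbered 2, titled "The role of stakeholders in the community-based actions in intervention clusters"). The HDT row includes "Guide data collectors to locate homes".
- **Who the HDTs are** (Protocol, Intervention). The women's support groups, called HDTs in the table and WDTs in the text, are one of three groups through which the package is delivered. The text states that "WDTs' main contribution to the intervention is actively identifying and connecting mothers and babies to essential standard care and emergency care". The project trains and supervises them. The table also has them teach mothers and tell the opinion leaders (COLs) and health extension workers (HEWs) which mothers and babies are missing care.
- **HDTs in both arms** (Protocol, Setting, Table 1): "Number of Health Developments Team | 545 | 560", intervention first.
- **Data sources** (Protocol, Data collection). Data are gathered "a maximum of five times at households and from health facility records". No deciding source is named for any outcome component.

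**The concern.** The blinding section separates those who measure from those who intervene. The role table then brings an intervention deliverer to the point of measurement and lists this among her roles in intervention clusters. The interview asks about the behaviours she was trained to promote. If she is at the door or within hearing, a mother may be inclined to say that she received the contacts or followed the advice. Such reporting would be expected to favour the intervention. If control clusters work differently, it would act in one arm only.

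The outcomes are not equally exposed. Antenatal contacts and facility delivery may be checked in facility records. Postnatal contacts, which HEWs may provide at home, and the newborn-care items (drying, skin-to-skin contact, breastfeeding, delayed bathing) probably rest mainly on what the mother says. Four postnatal contacts are part of the primary composite, so the primary comparison is touched as well as the newborn outcomes. Bias of this kind enters the recorded data, and a later analysis cannot readily remove it.

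**Working it through.** **1. The passages side by side**

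| Question | What the protocol states |
|---|---|
| Are collectors separate from the intervention? | Yes, and they "do not have formal information on which study arm the cluster to which they collect data belongs" |
| Who leads them to homes in intervention clusters? | HDTs, who deliver the intervention |
| Who leads them to homes in control clusters? | Not stated |
| Does the guide stay for the interview? | Not stated either way |
| Which source decides each outcome component? | Not stated; households and facility records are both used |

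The first two rows sit badly together. The last three leave open how large the problem is.

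**2. The plan's own benchmark**

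Inputs (Protocol, Sampling strategy and sample size): 20% against 30% completion, z-values 1.96 and 0.84, 150 mothers per cluster, ICC 0.01.

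- Individually randomised size: (1.96 + 0.84)² × (0.20 × 0.80 + 0.30 × 0.70) / 0.10² = 7.84 × 0.37 / 0.01 = 290.08 per arm.
- Design effect: 1 + 149 × 0.01 = 2.49.
- 290.08 × 2.49 = 722.3, rounded up to 723, the stated figure.

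The target effect is therefore 10 percentage points. The plan then recruits 1000 per arm.

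**3. Illustration of size**

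Assumptions: no true effect, 20% true completion in both arms, and a share f of intervention-arm non-completers wrongly recorded as completers. The documents give no value for f, so a range is shown.

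Apparent effect = (1 − 0.20) × f.

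For the false-positive rate, 1000 per arm in 10 clusters is 100 per cluster. The design effect is then 1 + 99 × 0.01 = 1.99, and the effective size is 1000 / 1.99 = 502.5 per arm. The rate is that of a two-sided 5% normal test of two proportions at that size.

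| f (assumed) | Apparent intervention rate | Apparent effect | False-positive rate |
|---|---|---|---|
| 0% | 20.0% | 0 points | 5.0% |
| 2% | 21.6% | 1.6 points | 9.6% |
| 5% | 24.0% | 4.0 points | 33.4% |
| 10% | 28.0% | 8.0 points | 84.5% |

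At f = 0.10 / 0.80 = 12.5%, misreporting alone would produce the whole planned effect.

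The table shows how sensitive the comparison is. It does not estimate the bias that this guide would cause.

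**The case against.** **The arm is not shown to be revealed.** A reader might infer that an HDT at the collector's side discloses the allocation. The documents do not support that. HDTs are a standing structure present in near-equal numbers in both arms (545 and 560). Disclosure needs a further fact, for example that control clusters use no such guide, or that she speaks of her trial role. This stands.

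**The asymmetry is not established.** The role table covers intervention clusters only, so it cannot show what happens in controls. It also lists screening and recruitment under HEWs, which must happen in both arms if 1000 women are enrolled in each. HDT guiding may likewise occur in both. This stands too: the finding is that no control procedure is stated, not that none exists.

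**The text says only that homes are located.** A reader might picture the volunteer at every round and in the room. The protocol says neither. It also does not require her to leave.

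**The blinding claim is modest.** Only formal information on the arm is denied, and the day-four interview asks about COL support, which can disclose the arm whoever guides the collector. So the fix would not secure masking. The reporting risk, however, does not depend on the collector knowing the arm.

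**The rates are assumed, and the composite is demanding.** A woman who missed several components would have to be misrecorded on all of them, including place of birth. Facility records may catch some of this. The upper end of the range is therefore not a likely value for the guide's effect on the composite. The objection has less force for single newborn-care items and for women who lack only postnatal contacts.

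**Conclusion.** The concern holds in limited form. The protocol assigns people who deliver the intervention to guide data collectors in intervention clusters and states no matching procedure for controls. This weakens the independence claimed in the blinding section and creates an avoidable risk of differential reporting, mainly for home postnatal contacts and newborn-care items.

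The size is unknown. The 1.6, 4 and 8 points rest entirely on assumed rates of 2%, 5% and 10% with no true effect. They show only that small differential misreporting would matter against a 10-point target. It would go too far to conclude that the arm is revealed, that collector independence is lost, or that over-reporting will occur. Severity: should fix. Confidence: moderate.

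**What to change.** 1. Remove the guiding task from the HDT row of the role table.
2. State one home-location procedure, used identically in both arms.
3. Record the home location on the existing tablet form at round one, so that rounds two to five need no guide. A location is an identifier, so it should be removed with the others under the storage plan.
4. Where a guide is needed at round one, use the same kind of guide in both arms. She points out the house and leaves before the interview.
5. Require in both arms that no HEW, HDT or COL member is present at any interview, and record on the form who was present.

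The cost is a wording change in the protocol and field instructions, one or two extra form fields, and slightly longer home-finding at round one. No extra staff should be needed.
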